## Introduction

1

Anal fistula is a common anorectal disease, with an estimated prevalence of 0.2%.^[1]^ It is often followed with an infection that does not easily heal with medications alone. So far, operation is still the optimal method to cure anal fistula. High anal fistula (HAF) is 1 of the intractable diseases in colorectal surgery, and it is difficult to achieve both goals of eradicating anorectal sepsis and preserving anal function. In recent years, more and more sphincter-sparing techniques have been applied to the treatment of HAF, including seton,^[2,3]^ endoanal advancement flap,^[4]^ ligation of intersphincteric fistula tract,^[5,6]^ and video-assisted anal fistula treatment.^[7]^ Nevertheless, those techniques may result in high recurrence rates.^[8,9]^

Evidence suggested that cutting seton technique can be a definitive treatment for HAF.^[10,11]^ The mechanism by which a drainage seton acts is still not clear, but by chronic strangulation, drainage, and stimulation, the technique can preserve the anal function as much as possible. However, the traditional cutting seton technique often needs 2 or even several times to tighten the thread. Because of the abundant nerves in the anal region, tightening the seton brings great pain to patients, which affects the clinical application of the therapy. In addition, it may lead to difficulty in controlling anal fluids and gas because of the larger scar left and the local defect in the anal after the operation.

Therefore, we propose an innovatively modified seton cutting technique for the treatment of HAF after long term attempts. In the procedure, a drainage seton is rerouted around internal anal sphincter to divide it slowly in the first stage, then loosely tighten the seton to promote the fibrosis of the anorectal ring when the granulation tissue grows close to the seton area in the middle stage, and incised the anorectal ring with a scalpel at last. The procedure could significantly reduce the pain when tightening the seton, shorten the healing time, and effectively shrink the scar, and preserve the anal function. The aim of our present study is to compare the difference of anal function, healing time, pain severity, recurrence, and complications between the procedure of the modified seton cutting technique and the conventional seton cutting technique against HAF with a randomized, controlled, prospective study.

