#### Intervention group

2.4.1

The procedure of the modified seton cutting technique will be performed with the following procedure:

(1)Make sure the position of internal ostium and the path of the fistula and its relationship with the sphincter by digital examination combined with preoperative intracavitary B-ultrasound or MRI;(2)From the posterior triangular approach of the anal canal, under the guidance of the probe, incise the skin and subcutaneous tissue along the fistula canal 2 cm above the anal margin to expose the posterior rectal space;(3)Explore the internal ostium and place a rubber seton, and tight the seton after the operation;(4)Properly trim the edge of the skin to maintain smooth drainage, and completely stop bleeding;(5)After the operation, when the granulation tissue grows close to the seton area, slightly tighten the seton and then hang it on the wound surface. After the granulation tissue growing close to the seton area again and the area becoming fibrosis, and the second formation of the anorectal ring, directly incise the seton area under local anesthesia.

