#### Control group

2.4.2

Cutting seton technique will be performed with the same procedure with the following procedure:

(1) to (4): The first 4 steps are the same with that in treatment group

(5) After the operation, when the granulation tissue grows close to the seton area, tighten the seton once and every 7 days according to the patient's tolerance to pain and the operator's clinical experience, until the rubber band falls off and the tissue is completely cut.

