### Outcome variables

2.5

The primary outcomes of the study are the continence state after surgery as assessed with Wexner incontinence score,^[14]^ and pain severity after tightening by Visual Analogue Scale. Secondary outcomes include complete healing of fistula, duration to healing, operation time, recurrence rates, and postoperative complications. All possible adverse events will be recorded, such as bleeding, anal stenosis, anal fissure, urinary retention, difficulty in defecation, urgency of stool, pelvic sepsis at any time. Patients will be followed-up at 1, 2, 3, 4 weeks, then every month in the outpatient clinic. At 6 months postoperatively, patients will be clinically assessed for recurrence of AF.

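### The pain primary is scored only after seton tightening, so it omits the incision that replaces repeated tightening in the modified arm and cannot compare pain between the two techniques

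*Protocol article*

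**What the plan says.** Section 2.5 (Outcome variables) names two primary outcomes: the Wexner continence score "and pain severity after tightening by Visual Analogue Scale". The section does not say which tightening counts, how long after it pain is scored, or how several scores in one patient are combined. The Methods part of the Abstract lists this outcome among those recorded at weeks 1, 2, 3 and 4 and then monthly.

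Section 2.4.2 (Control group) states: "The first 4 steps are the same with that in treatment group". Step 3, in section 2.4.1, includes tightening the seton after the operation, so every patient has one shared tightening. The arms separate at step 5:

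- Control (2.4.2): "tighten the seton once and every 7 days according to the patient's tolerance to pain and the operator's clinical experience", continuing "until the rubber band falls off and the tissue is completely cut". The Introduction adds that "the traditional cutting seton technique often needs 2 or even several times to tighten the thread".
- Modified (2.4.1): "slightly tighten the seton and then hang it on the wound surface". Later, once fibrosis has formed, "directly incise the seton area under local anesthesia". The Introduction describes this last stage as "incised the anorectal ring with a scalpel at last".

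No pain score is attached to the incision. Section 2.3 says that blinding does not apply to the operations; only the person doing the analysis is unaware of the groups.

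**The concern.** The Abstract and the Introduction give the aim as comparing pain severity between the two procedures. The modified technique trades repeated tightening for fewer, lighter tightenings and a final incision. An outcome tied to tightening observes the side of that trade where the benefit is expected and not the side where a cost could fall. If pain is lower at tightening but returns after the incision, the outcome would report a benefit all the same.

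This is a primary outcome, reported by patients who know their operation, so a positive result would carry much of the trial's conclusion. A statistical analysis plan can choose how to summarise the scores collected. It cannot recover pain after the incision if that pain was never scored.

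**Working it through.** **1. The plan's own figure.** The stated sample size comes from incontinence rates (25.5% and 10%, two-sided α 0.05, power 80%), not from pain. With unpooled variance:

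n = (1.960 + 0.842)² × (0.255×0.745 + 0.10×0.90) / (0.255 − 0.10)² = 7.849 × 0.279975 / 0.024025 = 91.5, rounded up to 92 per group.

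This agrees with section 2.6. The concern disputes no stated figure; 92 per group is used below only as the number analysed.

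**2. Events by arm, from sections 2.4.1 and 2.4.2.**

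| Event | Modified | Control | Covered by the pain primary? |
|---|---|---|---|
| Tightening at step 3 | 1 | 1 | Yes, as worded |
| Tightening at step 5 | 1, slight | 1, then every 7 days until the band falls off | Yes |
| Incision under local anaesthesia | 1 | 0 | No |

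With 2 control tightenings at step 5 (the lower figure in the Introduction), the tightening count is 3 control against 2 modified. With 4 (an assumption) it is 5 against 2.

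**3. What the unequal count alone can do.** Assumptions not in the documents: pain per event is the same in both arms, with mean 5, between-patient SD 1.5 and within-patient SD 1.5; 92 per arm; each patient is represented by the worst score. The expected maximum of k standard normal values is 0.564 for k = 2, 0.846 for k = 3 and 1.163 for k = 5; the variances are 0.682, 0.560 and 0.448.

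- 3 against 2: gap = 1.5 × (0.846 − 0.564) = 0.42 points. SE = √[2.25 × (2 + 0.682 + 0.560)/92] = 0.28. Ratio 1.50, so a two-sided 5% test rejects in about 32% of trials.
- 5 against 2: gap = 1.5 × (1.163 − 0.564) = 0.90 points. SE = √[2.25 × (2 + 0.682 + 0.448)/92] = 0.28. Ratio 3.25, so rejection is about 90%.

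Simulation with scores limited to 0–10 agrees: 0.4 points and 33%; 0.9 points and 90%.

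**4. The same set-up with other summaries.** With the first score or the patient's mean score, the expected gap is 0 and rejection stays near 5%.

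**5. Counting the incision.** If the incision is scored and assumed as painful as a tightening, the modified arm has 3 events against 3 in the control arm. The two worst scores then have the same distribution: gap 0, rejection 5%. The equal-pain assumption is only for illustration; the documents say nothing about the size of post-incision pain.

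**The case against.** The other side has several good arguments.

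- **Fewer and gentler tightenings are the intervention.** The Discussion names less pain during tightening as a hoped-for benefit, and the outcome measures that. This stands: part of any difference would be real. It does not meet the broader aim of comparing pain between procedures.
- **The direction of any tilt is not settled.** Control tightening is adjusted to the patient's tolerance, which could hold control scores down. This stands.
- **The incision is done under local anaesthesia.** That covers the cut itself; pain afterwards is not documented either way. So the size of the omission is unknown.
- **The summary of repeated scores may be fixed in a document not shown.** This stands for the calculation in steps 3 and 4, which depends on that choice. It does not stand for the incision, because the outcome definition itself leaves it out.

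A reader might also infer more than the text supports. One inference is that a single light tightening is compared with several. Step 3 tightens the seton in both arms, so the modified arm has two. Counting step 5 only (2 against 1) would give 0.8 points and 80% rejection, but section 2.5 does not limit scoring to step 5. Another is that some patients lose the seton before any tightening and have no value; no section describes this, and step 3 tightens everyone. A third is that the arms are recorded on different clocks. The Abstract sets common visits, and the first tightening at step 5 has the same trigger in both arms; timing differs only from the second onward.

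**Conclusion.** The concern holds in a limited form. As defined, the pain primary covers the step that the modified technique cuts back and omits the step put in its place. A lower score would show less pain after tightening, not less pain from the technique.

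It would go too far to say that the definition alone must produce a pain benefit, or that the comparison is known to favour the modified arm. The gaps of about 0.4 points (33% rejection) and 0.9 points (90%) need a worst-score summary that the article does not state, together with the assumed mean, SDs and tightening counts. With a mean or first score that part is zero. The omission of the incision remains under every summary, and its size cannot be derived from the documents.

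**What to change.** Define the pain primary on the visit schedule that both arms already share (weeks 1 to 4, then monthly). At each visit, ask every randomised patient for a VAS score of worst pain since the last visit, and make one stated per-patient summary of these scores the primary, for example the mean over a named period. The period must be the same in both arms and long enough to include the incision, whose timing the article does not give. On that measure a difference caused by more painful events is a genuine difference in burden, because the events of both arms count.

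Keep pain after procedures as a secondary outcome, scored after each tightening and also after the modified arm's incision.

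Cost: one VAS line on existing visit forms, a score after the incision, and revised outcome wording, with no extra visits and no change to treatment. The drawback is recall over the visit interval, which is longest after week 4, when visits become monthly.

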### Sample size calculation

2.6

According to previous literature^[15]^ that reported fecal incontinence to occur in up to 25.5% of patients with AF after cutting seton technique. Presuming that the rate of fecal incontinence after the operation of the modified seton cutting technique will be 10%, and taking α of 0.05 and β of 0.2, a sample size of 92 in each group will be needed. In order to compensate for loss to follow-up, 204 patients will be ultimately included.

### Statistical methods

2.7

Data will be analyzed by SPSS version 22(Created by IBM Corporation, New York, America). Statistical testing is 2-sided and *P* < .05 is considered statistically significant. Continuous data are expressed in of mean ± standard deviation, or median (quartile), and categorical variables as number and percentage. Student *t* test will used for normally distributed data and Mann–Whitney *U* test for non-normally distributed data. Fisher test or Chi-squared test will be used to analyze categorical data.

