**Methods::**

204 participants in this trial will be randomly divided into treatment group (procedure of the modified seton cutting technique) and control group (cutting seton technique) in a 1:1 ratio. The outcomes of continence state, pain severity after tightening, complete healing of fistula, duration to healing, operation time, recurrence rates, and postoperative complications will be recorded at 1, 2, 3, 4 weeks, then every month in the outpatient clinic. Data will be analyzed by SPSS version 22.

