## Discussion

3

At present, in the surgical treatment of HAF, cutting seton drainage is still the main surgical procedure. By cutting the sphincter slowly with the unique elastic cutting action of the seton, it could induce inflammatory fibrosis, avoid the sphincter retraction and separation, and prevent anal incontinence when the sphincter is momentarily severed.^[11]^ However, there are still some shortcomings according to literature reports.^[16,17]^ First, the pain in the treatment process is severe, because of continuously cutting the fistula and the anal sphincter by the elastic seton. Second, the healing time is longer, which needs about 40 to 50 days. Third, the left scar is large and obvious, which will affect the function of the anal sphincter, leading to incomplete anal incontinence.

The operation of the modified seton cutting is a modified technique of the conventional cutting seton, which could weaken the effect of chronic cutting. The modified technique is supposed to increase the cure rate, reduce the severe pain during the postoperative seton-tightening process, reduce local inflammation and scar, and shorten the healing time. Therefore, we try to conduct a clinical trial to compare the difference of anal function, healing time, pain severity between the procedure of the modified seton cutting technique and the conventional seton placement technique against HAF. However, we need to address several limitations in this protocol. First, the evaluator-blinded-only trial may lead to certain biases. Second, being a single institution study may affect the conclusions.

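### Duration to healing is time-to-event data, but the only tests named for it are the t test and Mann–Whitney, and the monthly visits straddle the expected healing time

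*Protocol article*

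**What the plan says.** Section 2.5 of the protocol article lists healing twice, once as an event and once as a duration: "Secondary outcomes include complete healing of fistula, duration to healing, operation time, recurrence rates, and postoperative complications". Healing time is also part of the aim in the Abstract and the Introduction.

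Section 2.7 gives one sentence for numeric data, "Student *t* test will used for normally distributed data and Mann–Whitney *U* test for non-normally distributed data", and one for the rest, "Fisher test or Chi-squared test will be used to analyze categorical data". It names no method for censored data and no rule for patients without a healing date.

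The Abstract says that the outcomes, duration to healing among them, "will be recorded at 1, 2, 3, 4 weeks, then every month in the outpatient clinic". Section 2.5 repeats the schedule. The Discussion says of the conventional technique that "the healing time is longer, which needs about 40 to 50 days".

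**The concern.** A duration to healing exists only for patients who heal while under observation. The article foresees patients who will not. It counts complete healing separately, hopes for a higher cure rate with the modified technique, and enlarges the sample for loss to follow-up. A t test or Mann–Whitney test on the recorded durations then compares healed patients with healed patients. Who heals may depend on the technique, so the comparison loses the protection of randomisation. It also cannot register a technique that leaves more fistulas open.

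The second matter is resolution. The healing time that the article itself expects in the control arm lies inside the longest gap of the early schedule. If the visit at which healing is first seen supplies the date, most patients in both arms get the same value. A difference of a few days, on an outcome in the trial's aim, is then hard to see.

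**Working it through.** **Group size.** The article states no figure for healing time, so the only number to reproduce is the 92 per group in section 2.6, which rests on incontinence. With unpooled variance, two-sided 0.05 and 80% power:

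n = (1.960 + 0.842)² × (0.255 × 0.745 + 0.10 × 0.90) / 0.155² = 7.849 × 0.280 / 0.0240 = 91.5, so 92.

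This agrees. The increase from 184 to 204 allows for 1 − 184/204 = 9.8% loss. The simulations below use 92 per group.

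**Inputs that are assumed.** The article gives no SD for healing time, no healed fraction and no healing time for the modified arm. I take normal times, a control mean of 45 days (the midpoint of 40 to 50), a range of SDs, and visits on days 7, 14, 21, 28, 60, 90 and so on to 180.

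**Step 1: unhealed patients left out.** Times among the healed are equal in both arms (mean 45, SD 8). The unhealed are censored at day 182 in the log-rank test.

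| Healed, control vs modified | Healed-only t test rejects | Log-rank on all rejects |
|---|---|---|
| 95% vs 95% | 5% | 5% |
| 95% vs 85% | 5% | 44% |
| 95% vs 80% | 5% | 77% |
| 90% vs 75% | 5% | 70% |

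The healed-only test does not react to a deficit of 10 to 15 points in healing.

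**Step 2: where the visits fall.** Week 4 is day 28 and the next visit is about day 58 to 60, so the whole of days 40 to 50 lies between two visits. For SD 7, the share first seen healed at day 60 is:

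- mean 45: Φ(15/7) − Φ(−17/7) = 0.984 − 0.008 = 0.976
- mean 40: Φ(20/7) − Φ(−12/7) = 0.998 − 0.043 = 0.955

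More than 95% of each arm share one date, and the true 5-day difference is recorded as about 1.6 days.

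**Step 3: power for 45 vs 40 days.** With exact dates, power ≈ Φ(5 / (SD × √(2/92)) − 1.96). At SD 10 this is Φ(5/1.474 − 1.96) = Φ(1.43) = 92%. The visit-dated figures are simulated t tests.

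| Assumed SD (days) | Exact dates | Dated by visit |
|---|---|---|
| 7 | over 99% | about 45% |
| 10 | 92% | 63% |
| 12 | about 80% | 57 to 60% |
| 15 | 61% | 50% |

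Runs differ by a point or two from simulation error. Placing the visit at day 58 instead of day 60 gives 54% at SD 7. For a 10-day difference (45 vs 35), power stays above 97% throughout. With equal true times and the same dating in both arms, the rejection rate stays at about 5%.

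**The case against.** Four points deserve a fair hearing.

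**Nothing says that unhealed patients are dropped.** Section 2.7 is a generic list, Mann–Whitney could keep unhealed patients at a worst rank, and rules for missing values may stand in a fuller document. That is right, so exclusion is a consequence of the tests as named, not a stated rule. The point stands because the article does fix the tests, and neither fits a duration that some patients lack.

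**The harm is partly visible elsewhere.** Complete healing has its own test. With 5% vs 15% unhealed, a chi-squared test flags the deficit in about 64% of simulated trials, more often than the log-rank test. This stands as mitigation, but it does not make the duration comparison a randomised one.

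**A reader might infer that the planned test often declares a worse technique faster.** With assumed healed times of 42 vs 45 days, SD 10, and 15% vs 5% unhealed, the t test rejects in about 48% of trials and the log-rank test in 10% to 12%. The 48% is power for a real 3-day difference among the healed, not a false-positive rate. With 10% unhealed in both arms the figures are about 48% and 20%, so much of the gap is test efficiency. The scenario also reverses the article's own expectation: "The modified technique is supposed to increase the cure rate".

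**A reader might infer unequal dating,** because control patients have their seton tightened every 7 days. The documents do not support this. Tightening in section 2.4.2 ends when the band falls off, section 2.4.1 implies extra contacts in the modified arm too, and nothing says that these contacts date healing. Nor does the article say that the visit date is the healing date, so the loss of power is conditional on that.

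**Conclusion.** The concern holds as a matter of a poorly fitting method and coarse timing on one secondary outcome. Followed as written, duration to healing is compared among patients selected after randomisation. Under the assumptions shown, that comparison misses a 10-point healing deficit that a log-rank test on all patients detects in about 44% of trials. If healing is dated by visit, power for a 5-day difference falls by roughly 11 to 55 percentage points over SDs of 15 down to 7. The loss is negligible for a difference near 10 days. It is a loss of power and not an inflated type I error, provided that dating is equal in both arms. The SDs, the healed fractions and the modified arm's healing time are all assumptions. The 40 to 50 days applies to the conventional technique only. The primary outcomes and the sample size are untouched, so this should be changed but does not threaten the trial's main result.

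**What to change.** In section 2.7, state that time from operation to complete healing will be analysed in all randomised patients by Kaplan–Meier curves with a log-rank test or Cox model, and that patients not healed will be censored at their last visit. If healing is dated by visit, add an interval-censored sensitivity analysis. This matters because simply using the scheduled visit date keeps the coarseness.

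In section 2.5, state how the healing date is obtained, in the same way for both arms, for example a date reported by the patient and confirmed at the next visit. Keep recurrence as its own outcome and do not fold it into failure to heal, since section 2.5 lists the two separately.

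The cost is small: a few sentences, one recorded date per patient and slightly more analysis work. SPSS, which the article names, has Kaplan–Meier and Cox; the interval-censored version may need other software. A log-rank test can also be less sensitive than a t test to a pure shift in healing times, as the 20% against 48% above shows. The curves should therefore be reported with the test.
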